#### Sample size

The sample size is to be calculated based on detecting the minimal, clinically relevant difference in the success rates of the three arms. Our preliminary study, which enrolled 145 patients, compared the efficacy of PRFG application (PRFG group) with drainage cessation (control group) when low output volume was achieved (<200 ml/d). During the 28-day treatment period, 77 % (58/75) of the patients in the PRFG group experienced fistula closure in comparison to 57 % (40/70) in the control group (*P* = 0.0127) [13]. The unpublished data of the pilot study demonstrated that closure rates were 80 % (60/75) in the PRFG group and 50 % (35/70) in the control group during the 14-day observation period. Due to the above raw data, the closure rates in the two treatment groups and one control group are assumed to be 80 % and 50 %, respectively. In this way, 51 patients per group are needed for this trial based on an alpha of 0.05, with a power of 90 %. Taking into account a drop-out rate of 10 %, a total sample size of 171 patients would be included, with 57 participants in each group.

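### The pilot's 14-day PRFG closure count (60/75), which supplies the 80% planning rate, exceeds its 28-day count (58/75); the counts need reconciling and the 90% power restating

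*Protocol article*

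**What the plan says.** All the figures are in the Sample size section of the protocol article.

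- The pilot's size: "Our preliminary study, which enrolled 145 patients".
- The published result, introduced by "During the 28-day treatment period": 77%, that is "58/75) of the patients in the PRFG group experienced fistula closure", against 57%, that is "40/70) in the control group", with P = 0.0127.
- The unpublished 14-day result: 80%, "60/75) in the PRFG group and" 50%, "35/70) in the control group during the 14-day observation period".
- The planning rates, said to follow from these data: 80% in each glue arm and 50% in control.
- The resulting size: "51 patients per group are needed for this trial based on an alpha of 0.05" and 90% power. With 10% drop-out this becomes 57 per group and 171 in total.

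**The concern.** A patient whose fistula closed within 14 days has also had a closure within 28 days. With one cohort and one definition, the 28-day count must therefore be at least as large as the 14-day count. The control arm behaves this way (35, then 40, of 70). The PRFG arm does not (60, then 58, of 75).

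The larger PRFG count is the one used for planning. It gives a 30-point difference, and the article offers no other basis for the 80%. If the true 14-day count is lower, the power stated for 51 per group is too high, and a null result would look more conclusive than the pilot data justify.

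**Working it through.** **Inputs** (Sample size section): pilot counts 60/75 and 35/70 at 14 days, 58/75 and 40/70 at 28 days; alpha 0.05; power 90%; 51 per group, 57 after 10% drop-out. The article does not say whether alpha is one- or two-sided. Two-sided is assumed here because it reproduces the stated size (one-sided gives 42).

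**1. One cohort?** 75 + 70 = 145, the stated enrolment, and both results use these denominators. The article says preliminary study for one result and pilot study for the other, but describes no second cohort.

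**2. Which count is doubtful?** Fisher's exact test on 58/75 versus 40/70 gives P = 0.0127, the printed value. The 28-day counts therefore agree with their own P value, and doubt falls on the 14-day PRFG count.

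**3. The plan's own figure.** The pooled two-proportion formula is

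n = [1.960·√(2·p̄·q̄) + 1.2816·√(p₁q₁ + p₂q₂)]² / (p₁ − p₂)²

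With p₁ = 0.80, p₂ = 0.50 and p̄ = 0.65:

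n = [1.960·√0.455 + 1.2816·√0.410]² / 0.09 = (1.322 + 0.821)² / 0.09 ≈ 51.0

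The unrounded value is 51.01, so strict rounding up gives 52; the arcsine formula gives 50.7, hence 51. Power at 51 is 90.0%. Drop-out: 51/0.9 = 56.7, so 57, and 3 × 57 = 171. The arithmetic is reproduced.

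**4. PRFG capped at 58/75 = 0.7733, control 0.50.** Here p̄ = 0.6367 and the difference is 0.2733.

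Power = Φ{[0.2733·√n − 1.960·√0.4626] / √0.4253}

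- n = 51: Φ{(1.952 − 1.333)/0.652} = Φ(0.949) = 82.9%
- n = 57: Φ{(2.064 − 1.333)/0.652} = Φ(1.120) = 86.9%
- For 90%, n = 63 per group

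**5. Three-group chi-square test (2 df) on closure rates**, with both glue arms at 0.7733 and control at 0.50. The mean rate is 0.6822, and the non-centrality is n·Σ(pᵢ − p̄)²/(p̄q̄) = n × 0.0498/0.2168.

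- n = 51: non-centrality 11.7, power 87.5%
- n = 57: non-centrality 13.1, power 91.0%

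**6. Summary**

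| PRFG vs control | Pairwise, 51 | Pairwise, 57 | 2 df, 51 | 2 df, 57 | n per group for 90%, pairwise |
|---|---|---|---|---|---|
| 80% vs 50% (plan) | 90.0% | 93.0% | 93.8% | 96.0% | 51–52 |
| 77.3% vs 50% (cap) | 82.9% | 86.9% | 87.5% | 91.0% | 63 |
| 75% vs 50% (illustration) | 74.9% | 79.5% | 79.7% | 84.2% | 77 |
| 77.3% vs 57.1% (28-day rates, sensitivity only) | 58.6% | 63.5% | 63.3% | 68.5% | 112 |

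**The case against.** The strongest reply is that an unstated definition could reconcile the counts. The Interventions section defines closure by drainage falling to zero, with confirmation by computed tomography at follow-up visits, and the Outcomes section lists recurrence separately. If the pilot's 14-day figure counted fistulas that had stopped draining and its 28-day figure counted only closures that had held, 60 followed by 58 is possible. This stands as a possibility, so a reader who infers that 60/75 is impossible, or that 80% has been shown to be wrong, goes further than the documents allow. But the article states no such difference. If there was one, it must still say which definition the 80% follows, because the Outcomes section of this trial requires confirmed complete closure.

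A reader might also take 83% as the most power the trial can have. It is not a bound. It assumes 51 evaluable per group, a pairwise test and control at exactly 50%. With 57 per group it is 87%. The Statistical analysis section refers to a Pearson chi-square test among the three groups; applied to closure rates with all 57 per group, that has 91% even at the capped rate. The control rate comes from the same unpublished data; at 45%, pairwise power with 51 per group would be about 93%.

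A third tempting reading is that the trial really has about 59% power. That figure applies 28-day rates to a 14-day endpoint. The controls had 14 more days to close spontaneously, and nothing in the article makes those the planning rates.

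Finally, the discrepancy is two patients in 75, and the Wilson 95% interval for 60/75 is about 70% to 87%, so 77.3% lies well inside ordinary planning uncertainty. That limits the size of the problem. It does not remove the contradiction, because the article presents the rates as following from the pilot data.

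**Conclusion.** The point holds as an unexplained contradiction in the input to the sample size; the calculation itself is not in error. On the natural reading (one cohort, cumulative closure, one definition), 60/75 at 14 days and 58/75 at 28 days cannot both be right, and the 90% power stated for 51 per group is not supported by the pilot. With PRFG capped at 77.3% and control at 50%, pairwise power is about 83% with 51 per group and 87% with 57; the three-group test has about 88% and 91%. The loss is thus about 7 percentage points for the comparison as planned (90.0% to 82.9%), and less with the full sample or the three-group test. These figures assume two-sided alpha 0.05 and, for the three-group test, the same rate in both glue arms, as the plan does. The cap is the highest 14-day PRFG rate compatible with the 28-day count, so a lower true rate would reduce power further. The documents do not settle which explanation is correct.

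**What to change.** 1. Check the pilot source data, and correct the 14-day counts or explain them under this trial's closure definition. If the two pilot figures used different definitions or cohorts, say so.
2. Restate the planning rates from the reconciled counts, and give the power that the fixed 171 patients deliver, naming the test, the sidedness and the number per group. Keep the 90% only if the reconciled rates and the named test support it. Until then, the capped case can be shown as 83% and 87% (pairwise, 51 and 57 per group) and 88% and 91% (three-group test).
3. If the 28-day rates are shown, label them as a sensitivity case only.

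The cost is a look-up in the pilot data and one paragraph of protocol text. No extra enrolment is asked for. The stated power may become slightly less favourable.

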### Assignment of interventions

#### Coordination

A clinical coordinating center in each participating site is established to identify subject eligibility for the study and to provide support to investigators and study personnel throughout the study period. The coordinating center consists of a principle investigator and a well-trained study coordinator. Research coordinators are required to screen all fistula patients in each study center for eligibility once a day, either the morning or afternoon. The patient cannot be enrolled until their eligibility is confirmed by the treating physician. Then, the study coordinator will obtain written informed consent from the patient. Patients will be consecutively enrolled at each of the participating centers whenever a study coordinator is available for enrollment. Consent will be obtained from participating clinicians before or at the time of patient consent.

#### Allocation

Subjects approved for randomization because they meet full eligibility criteria will be randomly assigned to one of the following study groups by using the Internet-based randomization software RANDOULETTE™ (Institute of Medical Information Sciences, Biometry and Epidemiology, University of Munich). Stratification for age will be performed, and an equal distribution between treatment arms (ratio of 1:1:1) will be warranted. The principle investigator in each coordinating center informs clinicians of the allocation sequence via a central telephone to ensure concealment.

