### Data collection, management and analysis

#### Data collection and management

A case report form is used to collect the data for each patient. Assessments are made at the screening period, inclusion (D0) and on days 1 to 14. Assessments include fistula assessment (location, output, duration, and length of fistula tract), monitoring (drainage, catheter, tubes, and adverse events), laboratory tests (hematology, biochemistry, urinalysis, and pregnancy test at inclusion only), and microbiology (blood cultures and cultures of isolates from fistula tracts). Data on adverse events, compliance and concomitant treatments are collected at each visit. Participants will be evaluated every day until the 14th day after randomization. Physicians and research nurses who are not involved in the patients’ care will assess the outcome.

All documents collected in this study will be stored safely in confidential conditions. On all study-specific documents, other than the signed consent, the participant will be referred to by the study participant number/code, not by name. Study documentation will be archived for a period of 5 years after the study.

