#### Statistical analysis

The intention-to-treat approach is utilized to examine differences in the fistula closure time among the three groups in the primary analysis by the Pearson χ2 test. Safety parameters and secondary efficacy parameters will be analyzed using the Pearson χ2 test and logistic regression (if necessary). Cox proportional hazards models and the Kaplan-Meier method will also be applied. Adverse events will be tabulated according to randomized group assignment and the proportions will be compared using Fisher’s exact test.

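### Randomisation is stratified by age, but the named primary test is an unstratified Pearson chi-square, so the primary analysis ignores the one factor used to constrain allocation

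*Protocol article*

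**What the plan says.** The Allocation section of the protocol article states "Stratification for age will be performed" and, for the allocation ratio, that "an equal distribution between treatment arms (ratio of 1:1:1) will be warranted". Age is the only stratification factor it names.

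The Statistical analysis section sets the primary intention-to-treat comparison as "differences in the fistula closure time among the three groups in the primary analysis by the Pearson χ2 test". It names no stratum or covariate for that comparison. For safety and secondary efficacy parameters it says they "will be analyzed using the Pearson χ2 test and logistic regression (if necessary"). It then adds "Cox proportional hazards models and the Kaplan-Meier method will also be applied", without saying whether these bear on the primary comparison.

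The Data collection and management section lists, among the data recorded, "fistula assessment (location, output, duration, and length of fistula tract"), and says "Assessments are made at the screening period, inclusion (D0) and on days 1 to 14". Baseline output and tract length should therefore be available for every patient.

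**The concern.** Stratified allocation forces the arms to be nearly equal in age mix. If age affects the chance of closure, that balance removes the between-stratum part of the variation from the true sampling variance of the treatment difference. An ordinary Pearson chi-square still uses the total variance, with the between-stratum part included. Its standard error is then too large, its true type I error falls below the nominal 5%, and some power that the design has already paid for goes unused.

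At stake is a modest loss of efficiency and an analysis that does not follow its own randomisation. A false positive finding is not at stake.

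**Working it through.** **1. The plan's own figure.** Inputs from the Sample size section: closure 80% in each glue arm and 50% in control, alpha 0.05 (taken as two-sided), power 90%, 51 per group, 10% drop-out, 171 in total. Two-proportion formula with pooled variance and mean rate 0.65:

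n = [1.960·√(2·0.65·0.35) + 1.2816·√(0.80·0.20 + 0.50·0.50)]² / 0.30² = (1.3221 + 0.8206)² / 0.09 = 51.01.

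This is 52 if rounded up, and power at the stated 51 is 89.99%. Then 51/0.90 = 56.7, so 57 per group, and 3 × 57 = 171. The plan's figures reproduce. The calculation is itself unadjusted.

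**2. Assumption.** The article gives neither the age cut-points nor any effect of age on closure. I take two age strata of equal size and vary the odds ratio (OR) for closure between them from 1 to 10. All checks compare one glue arm with control.

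**3. Closed form for type I error (50% closure in both arms).** The stratum rates are p = √OR/(1+√OR) and 1 − p. The ratio of within-stratum to total variance is r = p(1−p)/0.25 = 4√OR/(1+√OR)². Under stratified allocation the unadjusted statistic has standard deviation √r, so the true type I error is 2[1 − Φ(1.960/√r)].

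- OR 2: r = 0.971, 1.960/√r = 1.989, error 4.7%.
- OR 3: r = 0.928, 1.960/√r = 2.034, error 4.2%.
- OR 5: r = 0.854, 1.960/√r = 2.121, error 3.4%.

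**4. Simulation (200,000 runs per setting).** The unadjusted chi-square is compared with Cochran-Mantel-Haenszel (CMH) stratified by age. Type I error is at 57 per arm, 50% v 50%. Power is at 51 per arm, 80% v 50%. The last column is the true standard deviation of the risk difference divided by its mean unadjusted standard error, at 80% v 50%.

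| Age OR | Type I, unadjusted | Power, unadjusted | Power, CMH | Gain (points) | True SD / unadjusted SE |
|---|---|---|---|---|---|
| 1 | 4.9% | 90.24% | 90.12% | −0.1 | 1.01 |
| 1.5 | 4.7% | 90.41% | 90.39% | 0.0 | 1.01 |
| 2 | 4.6% | 90.44% | 90.65% | 0.2 | 1.00 |
| 3 | 4.1% | 90.93% | 91.73% | 0.8 | 0.98 |
| 5 | 3.3% | 91.53% | 93.23% | 1.7 | 0.95 |
| 10 | 2.1% | 92.71% | 95.59% | 2.9 | 0.90 |

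The type I error of the CMH test stays at 4.8% to 5.0% throughout. At OR 2 the gain reads as 0.3 if the powers are first rounded to 90.4% and 90.7%.

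**5. A covariate not used in the stratification.** In the same simulation with simple randomisation, the unadjusted type I error stays at about 4.9% and the SD/SE ratio at about 1.01 at every OR tried. Accounting for such a covariate raises power (90.3% to 93.1% at OR 5), but the unadjusted standard error is correct without it.

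**The case against.** The strongest reply is that the consequence is small and that covariate choices belong in an analysis plan that is not shown. Much of this stands. No passage shows that age predicts closure. At an odds ratio of 2 or below nothing of practical weight is lost. The sample size is an unadjusted calculation, and in the simulation the unadjusted test's power stays at 90.2% or more. The covariate lists for the Cox and logistic models are ordinary analysis-plan detail. What does not stand is treating the primary test as an open matter: the article names it, and an analysis plan that stratified it would be changing that choice rather than filling a gap.

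A reader might infer more than the documents support:

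- **That intervals are also too wide for output, tract length or duration.** Step 5 shows otherwise: only the factor used to constrain allocation has this effect. A Pearson chi-square is in any case a test, and the section specifies no interval for the primary effect.
- **That stratifying lifts power from exactly 90%.** With closure of 80% v 40% across age strata (r = 0.833), stratified power is Φ(3.24/√0.833 − 1.96) = 94.4%. The unadjusted test also benefits from the balance, at Φ((3.24 − 1.96)/√0.833) = 92.0%. The gain is about 2.4 points, not 4. That scenario is an odds ratio of (0.8/0.2)/(0.4/0.6) = 6, which nothing in the article supports.
- **That adjustment is worth a stated share of extra patients.** The conversion 1/(1 − R²) belongs to linear models and does not carry over to Cox or logistic regression. The article gives no R².
- **That chance imbalance between the nine sites, or in output or tract length, is an error.** An unadjusted randomised comparison already allows for it in its type I error. A site term is a preference.

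**Conclusion.** The point holds as a mismatch between design and analysis. Allocation is stratified by age, and the named primary test ignores age. If age is prognostic, the test is conservative. For age odds ratios of 2, 3 and 5, the true type I error is about 4.6%, 4.1% and 3.3%, and about 0.2, 0.8 and 1.7 points of power are forgone. These figures rest on two equal age strata and a single glue-versus-control comparison. The three-group test was not simulated, though the same variance argument applies to it.

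The planned power is kept, and a positive result would not be called into question. The correction is worth making because it costs almost nothing, not because the trial is at risk. For baseline output and tract length the only possible benefit is power, of a size that the documents do not allow one to state.

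**What to change.** State in the Statistical analysis section that the primary intention-to-treat comparison is stratified by the age strata used at randomisation. If it remains a comparison of 14-day closure proportions, use a Cochran-Mantel-Haenszel test. If it becomes an analysis of closure time, use a log-rank test or Cox model stratified by the same age strata. Whether a chi-square test suits a closure time at all is a separate question, and changing to an unstratified log-rank test would leave the present mismatch in place.

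Optionally, pre-specify baseline 24-hour output and tract length as covariates for precision. Adjusted Cox and logistic effects are conditional on the covariates and differ from the unadjusted effect, so state in advance which is primary.

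The cost is a change of wording, made before comparative results are examined and handled under the protocol's amendment procedure. The age stratum is already known at randomisation, and output and tract length are already collected. No new data or patients are needed.

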#### Blinding

No blinding will take place in this study. Eligible patients who have given consent will be randomized into any of the three groups.

### Data collection, management and analysis

#### Data collection and management

A case report form is used to collect the data for each patient. Assessments are made at the screening period, inclusion (D0) and on days 1 to 14. Assessments include fistula assessment (location, output, duration, and length of fistula tract), monitoring (drainage, catheter, tubes, and adverse events), laboratory tests (hematology, biochemistry, urinalysis, and pregnancy test at inclusion only), and microbiology (blood cultures and cultures of isolates from fistula tracts). Data on adverse events, compliance and concomitant treatments are collected at each visit. Participants will be evaluated every day until the 14th day after randomization. Physicians and research nurses who are not involved in the patients’ care will assess the outcome.

All documents collected in this study will be stored safely in confidential conditions. On all study-specific documents, other than the signed consent, the participant will be referred to by the study participant number/code, not by name. Study documentation will be archived for a period of 5 years after the study.

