When receiving glue sealing, the patients in the two treatment groups will have drainage cessation. Two main components of FG are placed separately in a double-syringe system with distal mixing catheter. When applied, equal amounts of fibrinogen and thrombin are mixed and the fibrin sealants are to form within 10 seconds. In order to assure total occlusion of the internal hole, the full length of the fistula tract must be determined by image examination prior to the procedure or with assistance of endoscopy [16].

The glue-sealing procedure could be repeated up to three times within the 14-day glue treatment period. A repeat sealing could be conducted if the fistula persists for 5 days after the first procedure. After the 14-day period, patients who fail to achieve medical closure are evaluated to further exclude possible factors disturbing healing, such as infection, foreign body, *etcetera.* These unhealed fistulas will either be treated by definitive surgery or continue to be treated conservatively based on the patient’s best interest and the physicians’ discretion.

Once glue sealing is applied, parenteral nutrition that provides calories of 20 to 25 kcal/kg is initiated through the peripheral vein or central venous catheter. Fistula drainage will be evaluated every day until the drainage decreases to zero, which is defined as fistula closure [17]. It also needs confirmation by contrast enhanced computed tomography at each follow-up visit to verify the complete closure of internal and external openings of the fistula tract. When the closure is achieved, a nasointestinal tube is to be placed and the enteral feeding (2,000 ml/d) is restarted gradually. Other SOC measures can be conducted when needed.

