#### Outcomes

The primary outcome of the trial is fistula closure time (defined as the interval between the day of enrollment and day of fistula closure) during the 14-day treatment period. Fistula closure is defined as complete closure of the fistula tract and internal and external openings later, which will be confirmed by contrast enhanced computed tomography at each follow-up visit where there is no drainage or any sign of inflammation [17].

In addition to the primary outcome measure of fistula closure, secondary outcomes include closure rates up to 14 days, closure rates up to 180 days, fistula recurrence rates and the incidence of adverse events and severe adverse events up to 180 days (defined as an event that was fatal or life-threatening, led to additional hospitalization or disability or required an intervention to prevent one of these outcomes).

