## Discussion

To our knowledge, this is the first study to evaluate the safety and efficacy of both autologous and commercial fibrin glue sealing for patients with low-output fistulas. Currently, fibrin glue is indicated only in treating simple ECFs of low-output volume as a first line therapeutic option. Therefore, complex or high-output ECFs are excluded from this study. In addition, this study is designed as an open-label, three-arm study, with autologous and commercial fibrin glue in two treatment groups and drainage cessation for use as a placebo. Because the autologous fibrin sealants require blood donation from patients themselves, patient blinding cannot be conducted. Further, there is a possibility that spontaneous closure can be achieved for fistula patients. Therefore, the control group is being established for comparison of the efficacy and safety of the glue application. In this way, this study is designed as an open-label and three-arm study.

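### Blinding is ruled out for everyone on a reason that covers only patients, so CT confirmation and closure adjudication stay unmasked although staff independent of care are already assigned to them

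*Protocol article*

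**What the plan says.** The Blinding section states: "No blinding will take place in this study". The Trial design section says the same, and neither makes an exception for assessors or image readers. The Discussion gives the only reason: "Because the autologous fibrin sealants require blood donation from patients themselves, patient blinding cannot be conducted".

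On who judges the outcome, Data collection and management says: "Physicians and research nurses who are not involved in the patients’ care will assess the outcome". It does not say that they are unaware of the group.

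On what is judged, there are two layers:

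- Interventions gives the daily rule: "Fistula drainage will be evaluated every day until the drainage decreases to zero, which is defined as fistula closure". It then adds that CT confirmation is also needed.
- Outcomes requires the tract and both openings to be completely closed, which "will be confirmed by contrast enhanced computed tomography at each follow-up visit where there is no drainage or any sign of inflammation".

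Participant timeline lists outpatient visits at 1, 3 and 6 months. The primary outcome is closure time within 14 days. Closure rates up to 14 and up to 180 days are secondary outcomes.

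**The concern.** The open label is justified for patients and is then applied to everybody. Nothing in the article explains why the staff who assess the outcome, or whoever reads the CT, must know the group. Keeping assessment away from the treating team removes one motive for a favourable call. It does not prevent an assessor who knows the arm from reading an equivocal scan or a mildly inflamed opening differently in glue and drainage-cessation patients.

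Detection bias of this kind is at stake in the closure outcomes. The Background says that limits of the earlier nonrandomized study may have biased its conclusion, and gives this as the reason for the present trial. Randomization deals with selection into the arms, not with how closure is called afterwards. None of the analyses named under Statistical analysis can undo calls made with knowledge of the arm.

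**Working it through.** **Step 1. Which parts of closure need judgement.**

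| Element | Section | When | Room for judgement |
|---|---|---|---|
| Drainage falls to zero | Interventions | Daily to day 14 | Small: a collected volume |
| Closure declared by assessors | Data collection and management | Days 1 to 14 and later | Some |
| No sign of inflammation | Outcomes | Follow-up visits | Yes |
| Tract and openings closed on CT | Interventions; Outcomes | Follow-up visits | Yes |

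The only outpatient visits listed are at 1, 3 and 6 months. On that reading CT does not set the closure day within the 14 days. It confirms or overturns it later. The interpretive elements therefore bear most on 180-day closure and on whether a 14-day closure is upheld.

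**Step 2. The plan's own figure.** Inputs from Sample size: 80% versus 50% closure, alpha 0.05 (two-sided assumed, as sidedness is not stated), power 90%, 51 per group, 10% drop-out.

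- Pooled formula: n = [1.960 × √(2 × 0.65 × 0.35) + 1.282 × √(0.8 × 0.2 + 0.5 × 0.5)]² / 0.30² = 51.01, or 52 when rounded up.
- Arcsine formula: h = 2·arcsin√0.8 − 2·arcsin√0.5 = 0.6435; n = 2 × (1.960 + 1.282)² / h² = 50.7, or 51.
- Drop-out: 51 / 0.9 = 56.7, or 57 per group; 3 × 57 = 171.

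The stated size is reproduced, and masking does not change it.

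**Step 3. Illustration of what unmasked calls could do.** Assumptions, none of them from the documents: no true effect; true closure 50% in every arm (the plan's control rate); a share m of still-open glue fistulas called closed; no errors in controls.

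- Recorded glue rate = 0.50 + 0.50 × m. This gives 0.55 for m = 0.10 and 0.60 for m = 0.20.
- Error rate = sum over x and y of Bin(x; 57, recorded glue rate) × Bin(y; 57, 0.50), taken where the uncorrected statistic (x/57 − y/57)² / [p̄(1 − p̄) × 2/57] exceeds 3.84, with p̄ = (x + y)/114.

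| m | Recorded glue vs control | Pairwise test, 57 vs 57 | Three-group test, both glue arms affected |
|---|---|---|---|
| 0 | 50% vs 50% | 4.9% | 5.1% |
| 1 in 10 | 55% vs 50% | 8.1% | 8.2% |
| 1 in 5 | 60% vs 50% | 18.4% | 18.6% |

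**Step 4. Range.** With 51 per group and a normal approximation, the chance of a false result in favour of glue in one comparison rises from 2.5% to about 4.4% (m = 5%), 7.3% (10%), 17% (20%) and 33% (30%).

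**The case against.** The best counter-argument is that the primary endpoint is more objective than the concern suggests. Zero daily drainage is the working definition of closure and fixes the closure day, while CT and inflammation come in at later visits. This stands. A reader might infer that the primary endpoint as a whole is a subjective call; the Interventions section does not support that.

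The second argument is that the remedy reaches the closure day only weakly. Nursing staff collect the output volumes at the bedside and may know the arm. Coding the log afterwards masks the adjudicator, not the person who wrote down zero. This stands too and limits what the change can achieve.

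Third, the illustration is built on chosen error rates that run in one direction only, and the assumed shifts of 5 and 10 points are small beside the planned 30-point difference (80% versus 50%). That is correct: it shows sensitivity, not this trial's actual risk.

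Fourth, a reader might infer that the bias would run towards glue because the sponsor's own earlier study favoured it. The article describes that study as the authors' previous work and does not attribute it to the sponsor. It tested only autologous glue, so it offers no particular reason for leaning towards the porcine sealant. Bias in favour of glue is possible, not established.

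Finally, CT readers are not named, and image-reading procedures often sit in a full protocol. But the exclusion of blinding is stated outright and without exception, so this is a stated choice, not a detail left for elsewhere. The use of assessors outside the care team is a real safeguard, though an incomplete one.

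**Conclusion.** The point holds in a limited form. All blinding is excluded on a reason that applies to patients only, while independent assessors are already in place and could be masked for part of their work. The exposed steps are the declaration of closure, the judgement of inflammation and the CT confirmation. The outcomes most affected are 180-day closure and the confirmation of 14-day closures; the closure day itself is affected less.

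The documents do not show that bias occurred, or how large it might be. The rise from 4.9% to 8.1% or 18.4% depends on the assumed 1-in-10 and 1-in-5 misclassification, on no error in controls and on no true effect. Nothing here makes the open-label design illegitimate. This is a reducible risk that should be addressed, not a contradiction or a numerical error.

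**What to change.** Amend Trial design, Blinding, and Data collection and management to say three things:

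- The trial is open-label for patients and treating staff.
- CT reading and closure adjudication are done by the already planned independent assessors from coded images and drainage records, with the arm and all glue-procedure information (number and dates) removed.
- The masked call is the one used in the closure analyses.

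The scans, the daily drainage records, the assessors and participant codes on study documents are already planned. The added cost is the work of coding images and records, plus a formal amendment, since the article reports that recruitment is under way. CT images already taken could be re-read masked if they have been kept. The sample size stays at 171.

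The amendment should also state the limit openly: masking is partial, because drainage is still observed and recorded unmasked at the bedside, and glue may be visible at the external opening.
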